### **16.9 Amendments to the research**

Any substantial amendment made to the protocol by the coordinating investigator must be sent to the sponsor for approval. After this agreement, the sponsor must obtain a favourable opinion from the EC prior to its implementation.

The information sheet and consent form may be revised if necessary, particularly in the event of a substantial amendment to the research or the occurrence of adverse effects.

## 16.10 Final research report

The final report of the research involving human subjects mentioned in Article R1123-67 of the PHC is prepared and signed by the sponsor and the investigator. A summary of the report written according to the reference plan of the competent authority must be sent to the competent authority within one year, after the end of the research, corresponding to the end of the participation of the last person participating in the research.

## 16.11 Archiving

The specific documents of a research project involving human subjects at risk and minimal constraints will be archived by the investigator and the sponsor for a period of 15 years after the end of the research project.

In particular, this indexed archiving involves:

- The “research” folders for the Investigator and the sponsor including (non-exhaustive list):
  - The successive versions of the protocol (identified by the version number and version date)
  - the EC’s opinions
  - letters of correspondence
  - the inclusion list or register
  - the appendices specific to the research
  - Final research report
- The data collection documents

## 17 FINANCING AND INSURANCE

### 17.1 Source of funding

*ANRS – REACTing and the AP-HP*

### 17.2 Insurance

The Sponsor shall take out, for the entire duration of the research, insurance covering its own civil liability as well as that of any doctor involved in the conduct of the research. It also provides full compensation for the harmful consequences of the research to the person taking part and his/her beneficiaries, unless it can prove that the damage is not attributable to its fault or to any other party involved, without the possibility of invoking the act of a third party or the voluntary withdrawal of the person who had initially agreed to participate in the research.

Public Hospitals of Paris (AP-HP) has taken out insurance with the company HDI-GLOBAL SE through BIOMEDIC-INSURE, guaranteeing its civil liability as well as that of any participant (doctor or staff involved in conducting the research), in accordance with Article L.1121-10 of the PHC.

## 18 RULES REGARDING PUBLICATION

The rank of authors will be defined based on the effective contribution of each site referent to recruitment and each member of the scientific committee to the design, implementation of the study and writing of the article, according to rules that will be defined during the first meetings of study participants.

The ranking of authors will be as follows: [name] (first author), [name] (penultimate author), [name] (last author).

### **18.1 Mention of the AP-HP affiliation for the projects sponsored by the AP-HP**

The AP-HP will be mentioned in the affiliations of the authors of the publications that will result from this research and a copy of the publication will be sent to the DRCD.

- If an author has several affiliations, the order in which the institutions are cited (the AP-HP, University, INSERM, etc.) does not matter,
- Each of these affiliations must be identified by an address separated by a semi-colon,
- The AP-HP institution must appear under the acronym “AP-HP” first in the address followed precisely by: The AP-HP, hospital, department, city, postal code, France.

### **18.2 Mention of the sponsor the AP-HP (DRCI) in the “acknowledgements” of the manuscript**

The AP-HP (DRCD) will be mentioned as being the sponsor of the research as follows:

“The sponsor was Public Hospitals of Paris (Delegation for Clinical Research and Innovation)”

### **18.3 Mention of the funding body in the “acknowledgements” of the manuscript**

The project funding sources will be mentioned, as follows:

## **20 LIST OF ADDENDA**

**Addendum 1: List of participating sites and investigators**

**Addendum 2: Consultant's self-questionnaire**

**Addendum 3: Posters**

**Addendum 4: Information sheet for the consultant**

**Addendum 5: Information sheet for the consultant for the ancillary study**

**Addendum 6: DEPIST-COVID reference case questionnaire**

|                        |              |
|------------------------|--------------|
| Study                  | DEPIST-COVID |
| Promotion/gestion code | APHP201625   |
| Study coordinator      | [name]   |

## Final statistical analysis plan English version

### 1 FINAL ANALYSIS PLAN

#### 1.1 Description of planned statistical methods

##### Descriptive analysis

The characteristics of the sites and patients will be described. The proportion of patients tested positive for other respiratory viruses will be described. Qualitative data will be described by means of numbers and proportions, and quantitative variables will be described using means, standard deviations, ranges, medians and interquartile ranges. A flow chart presenting the population included and analysed will be presented.

##### Primary endpoint analysis

The primary endpoint is the proportion of patients tested positive for SARS-CoV-2 amongst the flow of consulting adults. The denominator is a number of patients in the emergency departments (and not the number of tests performed).

Patients considered positive for SARS-CoV-2 will be those with a positive test result and whose SARS-CoV2+ status is not known. Patients considered non-positive for SARS-CoV-2 will be patients not tested, patients tested negative or with an undeterminate result and patients tested positive with a known SARS-CoV2+ status.

The primary analysis will be performed according to the intent-to-treat (ITT) principle. The primary outcome will be analysed using a generalised linear mixed model (Poisson distribution or any other distribution adapted to the data) with the centre as a random intercept and the strategy, the period and the period x strategy interaction as fixed effects. The incidence of SARS-CoV2 or the evolution of the epidemic over time will be taken into account if appropriate. Fixed variables could be added to the model if appropriate.

##### Secondary endpoints analyses

- The proportion of patients tested positive for SARS-CoV-2 among the asymptomatic or paucisymptomatic patients tested by nurses and that in the Paris Metropolitan area at the same period will be compared using an asymptotic Wald test.  
The proportion obtained in each emergency department will be compared to that of the department's IRIS geographical area using an asymptotic Wald test. The same comparisons will be made across the entire tested population.
- The feasibility of the testing will be described: proportion of patients who have completed the questionnaire, proportion of offered, accepted and performed tests, and notified of the SARS-CoV-2 result and staff involved (nurses, caregivers, doctors, others),
- The proportion of patients tested positive for SARS-CoV-2 among the patients tested by nurses, the proportion of asymptomatic patients among the patients tested by nurses and the proportion of asymptomatic patients among the patients tested positive for SARS-CoV-2 will be described.

|                        |              |
|------------------------|--------------|
| Study                  | DEPIST-COVID |
| Promotion/gestion code | APHP201625   |
| Study coordinator      | [name]   |

- The symptoms of patients tested positive for SARS-CoV-2 will be described in the patients completed the questionnaire.
- Exposure factors will be described using the items in the DEPIST-COVID questionnaire. Among patients tested, the exposure factors associated with the positivity of the SARS-CoV-2 test will be analysed using a generalised linear mixed model (binomial distribution or other distribution adapted to the data). The exposure factors will be considered as fixed effects and the site as a random intercept. Other fixed variables could be added to the model if appropriate.
- The sociodemographic, behavioural and practical factors of diagnosed patients associated with positive SARS-CoV-2 infection will be described for the schemes (DEPIST-COVID, ComCor) according to the types of variables (proportion, mean and standard deviation or median, Q1-Q3) and presented with their 95% confidence interval. If appropriate, the factors will also be analysed in the population of DEPIST-COVID cases (positive tested patients) and controls (negative and matched tested patients).

URC-Est, AP-HP will be in charge of the analysis using SAS software, Version 9.4 (SAS Institute, Inc., Cary, NC) and R freeware, Version 4.1.3 (R Core Team, 2022).

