## 2.2 Research hypotheses

Our working hypotheses are that the systematic offering of SARS-CoV-2 screening by rapid emergency tests performed by nursing teams, combined with current diagnostic practice in patients with signs suggestive of Covid-19, would be superior to the control strategy and would allow:

- testing for rare or asymptomatic forms of SARS-CoV-2 infection, particularly in people who may escape other screening schemes, and thus improve the control of SARS-CoV-2 circulation in the Paris Metropolitan area, and compare the positivity rate among asymptomatic patients in the study to that of the Paris Metropolitan area region, while expecting to obtain a higher rate in the emergency department population,

- to study the sociodemographic, behavioural factors and practices associated with SARS-CoV-2 infection in the population tested in the emergency department compared to those captured by other schemes (ComCor and COVISAN),
- estimating, by modelling, the incidence of new SARS-CoV-2 infections in the Paris Metropolitan area during the study period,
- to limit the risks of transmission of persons tested positive through the immediate and direct activation of the COVISAN scheme facilitating the steps of isolation, tracing, and source search.

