### 6.3.3 Intervention strategy

- A self-administered questionnaire (see addendum 2) on SARS-CoV-2 symptoms, contagion possibilities, situations at risk of exposure as well as socio-demographic characteristics will be offered to enrolled patients who are able to complete it. It was developed by the research team from other questionnaires currently used in France (SocialCov and ComCor questionnaires, Pasteur Institute) or elsewhere .
- The patient will fill out the questionnaire and submit it directly to the triage nurse (IOA), or the attending nurse at the time of care. If necessary, the nurse will complete the questionnaire with the patient.
- In the triage room or in a cubicle, SARS-CoV-2 screening will be offered by the nurse regardless of the answer to the questionnaire. According to the decree of 24/07/2020, nurses are authorised to perform, without medical prescription, nasopharyngeal sampling procedures for SARS-CoV-2 infection testing; trained caregivers are also authorised to do so under the responsibility of a physician or a qualified nurse from their institution.
- A nasopharyngeal sample for SARS-CoV-2 test will be taken in a cubicle by the nurse in compliance with the performance conditions and in particular the personal protection measures recommended in the hospital protocol, with the exception of patients who cannot have a nasopharyngeal sample (thrombocytopenia, ENT malformation). In case of contraindication to nasopharyngeal sampling, oropharyngeal sampling is indicated, according to the HAS recommendations . The choice of test will be determined based on the presence of suggestive symptoms.
- The patient will note agreement to participate in the study on page 1.
- A patient with one or more symptoms listed in the patient questionnaire will be considered symptomatic.
- A multiplex PCR test will be performed for patients with symptoms suggestive of SARS-CoV-2 infection, known as “symptomatic”, on medical advice. The analysis time is 75 minutes.
- For patients with no symptoms suggestive of SARS-CoV-2 infection, known as “asymptomatic”, an RT-LAMP test will be performed. The analysis time is 5 to 15 minutes.

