### 13.2 Description of the statistical methods

The analysis will be performed at the end of the research, after a data review meeting and freezing of the database. An analysis plan will be drafted and any changes will be documented.

The characteristics of the sites and patients will be described. The proportion of patients tested positive for other respiratory viruses will be described. Qualitative data will be described by means of numbers and proportions, and quantitative variables will be described using means, standard deviations, ranges, medians and interquartile ranges.

The primary analysis will be performed according to the intent-to-treat (ITT) principle. The primary outcome will be analysed using a generalised linear mixed model (Poisson distribution or any other distribution adapted to the data) with the strategy as a fixed effect, the centre x strategy interaction as a random effect and the centre as a random intercept.

For the other secondary outcomes:

- The proportion of patients tested positive for SARS-CoV-2 among the asymptomatic patients tested and that in the Paris Metropolitan area at the same period will be compared using an asymptotic Wald test.  
The proportion obtained in each emergency department will be compared to that of the department's IRIS geographical area using an asymptotic Wald test.  
The same comparisons will be made among the symptomatic patients tested and across the entire tested population.
- The feasibility of the testing will be described: proportion of patients who have completed the questionnaire, proportion of offered, accepted and performed tests, and notified of the SARS-CoV-2 result and staff involved (nurses, caregivers, doctors, others),
- The proportion of patients tested positive for SARS-CoV-2 among the patients tested, the proportion of asymptomatic patients among the patients tested and the proportion of asymptomatic patients among the patients tested positive for SARS-CoV-2 will be described in the 2 strategies.
- The symptoms of patients tested positive for SARS-CoV-2 will be described in both strategies and in the total population.

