### **Secondary endpoints analyses**

- Factors associated with performing systematic nurse-driven screening will be analysed in patients who had screening offer using a generalised linear mixed model (binomial distribution) with the centre as a random intercept and the patient characteristics as fixed effects.

- The factors associated with new SARS-CoV-2 diagnoses will be analysed using a generalised linear mixed model (binomial distribution) with the centre as a random intercept and patient characteristics as fixed effects.

- The proportions of new SARS-CoV-2 diagnoses through systematic nurse-driven screening overall and per ED, and proportion among all patients tested in EDs, will be compared to the proportion of positive tests among adults tested in the geographical departments of the Paris Metropolitan area using the Miettinen-Nurminen method for risk difference and 95% CI estimations.

[figure not shown]

Coller ici l'étiquette patient

N° DOSSIER :

\_\_\_\_\_  
Centre

\_\_\_\_\_  
Patient

PLEASE FILL OUT THIS QUESTIONNAIRE BY CHECKING THE SQUARE  
CORRESPONDING TO YOUR RESPONSE [figure not shown]

1 You are:

☐ male ☐ female

2 What is your date of birth?

Month Year

3 Do you have symptoms suggestive of Covid-19?

☐ Yes ☐ No

> If yes, please precise:

☐ Fever (>38°C)  
or fever sensation

☐ Cough

☐ Loss of smell

☐ Muscular pain

☐ Unusual fatigue

☐ Breathing difficulty  
(shortness of breath)

☐ Loss of taste

☐ Other

☐ Headache

☐ Sore throat

☐ Diarrhoea

☐ Runny nose

> If yes, date of first symptoms:

Day Month Year

4 What is your postcode?

5 In which country were you born?

☐ France

☐ Other

Please specify your country of birth:

6 Until what age did you study?

years

7 Currently (over the last month):

☐ You work

☐ You do not work

☐ You are seeking employment

☐ You are a student

> If you work:

• Do you work away from home?:

☐ Yes

☐ No

☐ Partially

• Does your occupation expose you to contacts with:

- Members of the public?

☐ Yes

☐ No

- Sick persons?

☐ Yes

☐ No

8 What is your medical coverage:

☐ Social security without supplementary health insurance

☐ CMU (Universal medical cover)

☐ Social security with supplementary health insurance

☐ AME (State medical assistance)

☐ No medical coverage

☐ Other

9 Do you suffer from a chronic disease (diabetes, high blood pressure, angina pectoris, chronic bronchitis, asthma or chronic respiratory disease)?

☐ Yes

☐ No

10 Do you currently smoke cigarettes?

☐ Yes

☐ No

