| Hospitalization                                                                              | .                            | 24 (1.8)                       | .                                    | 2 (5.6)                     | .                                       | 22 (1.7)                    | 3.9 (-0.3, 16.5)            |
| Only emergency department visit: outpatients                                                 | .                            | 1304 (98.2)                    | .                                    | 34 (94.4)                   | .                                       | 1270 (98.3)                 | -3.9 (-16.5, 0.3)           |
| Among patients with rapid multiplex respiratory virus test, other respiratory viruses | 581                          | .                              | 116                                  | .                           | 465                                     | .                           | .                           |
| Yes*****                                                                                     | .                            | 77 (13.3)                      | .                                    | 5 (4.3)                     | .                                       | 72 (15.5)                   | -11.2 (-15.7, -5.2)         |

\* Patients with indeterminate results or a known positive SARS-CoV-2 status were not included in this table. In univariate analysis, factors associated with new infections diagnosed through screening for asymptomatic/paucisymptomatic patients were mainly older age, having mild symptoms, not being from France, particularly being from Sub-Saharan Africa, being unemployed, not having medical coverage, living in a community, being a case contact and not being previously screened.

\*\* Among patients who underwent a rapid molecular SARS-CoV-2 test, 258 (7.4%) reported having symptoms. Among patients who underwent a rapid multiplex respiratory virus test, 508 (90.1%) reported having symptoms.

\*\*\* Chronic diseases: diabetes, arterial hypertension, angina pectoris, chronic bronchitis, asthma or chronic respiratory disease

\*\*\*\* For this variable of the DEPIST-COVID questionnaire, data were collected in 8 centers, and it was not possible to collect them later in the remaining 10 centers. Findings are presented for 8 centers (n=1,510 patients, missing data: 12.1% in the 8 centers).

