#### Reference

Appendix J. Comparison of the proportions of new SARS-CoV-2 diagnoses through screening in emergency departments and of positive tests through community screening for individuals aged 18+ of the geographical departments of the Paris metropolitan area screened during the same period

- a. Table J1. New SARS-CoV-2 infections diagnosed through screening in emergency departments for asymptomatic/paucisymptomatic patients and positive tests through community screening for asymptomatic adults in the geographical departments of the Paris metropolitan area during the same period

| SARS-CoV-2 positive tests | Total population |                | SARS-CoV-2 screening for asymptomatic / paucisymptomatic patients in EDs |             | Community screening for SARS-CoV-2 in the Paris metropolitan area* |                | Risk difference (95% Confidence interval) |
|---------------------------|------------------|----------------|--------------------------------------------------------------------------|-------------|--------------------------------------------------------------------|----------------|-------------------------------------------|
|                           | N                | n (%)          | n                                                                        | n (%)       | n                                                                  | n (%)          |                                           |
|                           | 3404867          | .              | 4283                                                                     | .           | 3400584                                                            | .              | .                                         |
| Yes                       | .                | 156522 (4.6)   | .                                                                        | 224 (5.2)   | .                                                                  | 156298 (4.6)   | 0.6 (0.01, 1.3)                           |

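### The first secondary comparison sets an ED group that includes patients with symptoms against community tests in asymptomatic adults; without those patients the reported ED excess of 0.6 points disappears

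*Combined protocol and SAP*

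**What the plan says.** Protocol 13.2 defines the comparison for patients without symptoms: "The proportion of patients tested positive for SARS-CoV-2 among the asymptomatic patients tested and that in the Paris Metropolitan area at the same period". Protocol 6.3.3 draws the line strictly: "A patient with one or more symptoms listed in the patient questionnaire will be considered symptomatic". Protocol 2.2 states the direction expected for asymptomatic patients, "while expecting to obtain a higher rate in the emergency department population".

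The final SAP (section 1.1, Secondary endpoints analyses) changes the ED side: "The proportion of patients tested positive for SARS-CoV-2 among the asymptomatic or paucisymptomatic patients tested by nurses and that in the Paris Metropolitan area". It does not define paucisymptomatic. Section 1.5, which lists the main changes since the protocol, does not mention the widening. Neither this sentence nor the later Changes to the analysis plan says whether the community tests are those of people without symptoms. The later text has the ED proportion "compared to the proportion of positive tests among adults tested in the geographical departments of the Paris Metropolitan area using the Miettinen-Nurminen method".

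The comparator becomes visible only in Appendix J. The title of Table J1 describes it as "positive tests through community screening for asymptomatic adults in the geographical departments of the Paris metropolitan area during the same period". Table J1 reports 5.2% in the EDs and 4.6% in the community, a risk difference of 0.6 points (0.01 to 1.3). The text under Table J2 concludes that three EDs had a higher proportion than their geographical department.

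**The concern.** One side of the comparison admits patients with symptoms and the other, by its label, does not. Patients with symptoms are far more likely to test positive, so the mixture raises the ED figure for a reason unrelated to what ED screening finds among people without symptoms.

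This is the first-listed secondary endpoint and it tests a stated hypothesis. If the symptomatic fraction accounts for the excess, Tables J1 and J2 appear to support a hypothesis that the trial's own data do not support.

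**Working it through.** **Inputs**
- Table J1: ED 224 new diagnoses in 4,283; community 156,298 positives in 3,400,584.
- Table E1: 4,192 patients (224 new diagnoses, 3,968 negatives). Symptom status is known for 4,062 (216 and 3,846). Symptoms were present in 766 (133 and 633).
- Table D1: 4,283 screened; symptom status known for 4,148, of whom 794 had symptoms.
- Table J2: tests and new diagnoses per ED.

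**1. The reported figure.** 224/4,283 = 5.23% and 156,298/3,400,584 = 4.60%. The difference is +0.63 points, Miettinen-Nurminen 95% CI 0.006 to 1.34. This reproduces Table J1. The Wald interval, the method named in SAP section 1.1, is -0.03 to 1.30 and includes zero.

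**2. Split by symptom status (Table E1).**
- With symptoms: 133/766 = 17.4%.
- Without: (216 - 133)/(4,062 - 766) = 83/3,296 = 2.52%.
- Patients with symptoms are 766/4,062 = 18.9% of the group and supply 133/216 = 61.6% of its new diagnoses.

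**3. ED patients without symptoms against the community.** 2.52% - 4.60% = -2.08 points, Miettinen-Nurminen 95% CI -2.56 to -1.49, assuming independent observations.

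**4. Missing symptom status.** 4,192 - 4,062 = 130 patients: 224 - 216 = 8 positives and 3,968 - 3,846 = 122 negatives.
- Only the 122 negatives counted as asymptomatic: 83/3,418 = 2.43%.
- Only the 8 positives counted as asymptomatic: 91/3,304 = 2.75%.

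**5. Different numerators.** The ED side counts new diagnoses; the community column is labelled positive tests. The footnote to Table E1 says: "Patients with indeterminate results or a known positive SARS-CoV-2 status were not included in this table". That removes 4,283 - 4,192 = 91 patients, whom Table J1 keeps in its row of non-positives. Taking Table E1 as a subset of the screened column of Table D1:
- with symptoms: 794 - 766 = 28;
- without: (4,148 - 794) - 3,296 = 3,354 - 3,296 = 58;
- status unknown: 91 - 28 - 58 = 5.

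If all 58 were positive, the ED rate would be (83 + 58)/3,354 = 141/3,354 = 4.20%. The difference is then -0.4 points (Miettinen-Nurminen -1.0 to 0.3). If the 5 excluded patients and the 8 positives of unknown status are also counted as asymptomatic positives, it is (83 + 58 + 5 + 8)/(3,296 + 58 + 5 + 8) = 154/3,367 = 4.57%, a difference of -0.02 points. Equality needs 3,354 x 0.04596 - 83 = 71 extra positives, against the 58 patients known to be without symptoms.

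**6. Clustering.** From Table J2, with k = 18 EDs, n_i tests, x_i diagnoses, N = 4,283 and p = 0.0523, the design effect is [k/(k-1)] x sum(x_i - p n_i)^2 / [N p(1-p)] = 8.3. It is 3.6 without centre 15. Applied to step 3, the standard error is sqrt(0.0252 x 0.9748/3,296) x sqrt(8.3) = 0.27 x 2.88 = 0.79 points. With t on 17 df the interval is -3.7 to -0.4. This borrows the design effect of the mixed group, because no per-ED counts by symptom status are given.

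**The case against.** Four points can fairly be made against this.

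First, a reader might infer that the SAP itself prescribes an asymptomatic community comparator. It does not, and protocol 13.2 is not explicit either; the word comes from Appendix J. What stands is a gap in the plan plus a mismatch in the tables, and both must be cited.

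Second, a reader might take 2.5% against 4.6% as a full like-for-like result showing that ED positivity is lower. The documents do not support that. Symptom status is matched but the numerator is not, and step 5 shows that aligning it could close most or all of the gap. That bound is extreme, because the 91 exclusions include indeterminate results, but the documents do not say how many. They also do not say how the community source defined asymptomatic.

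Third, Table J1 names both populations and Table E1 publishes the symptom split, so nothing is hidden. The comparison is external, non-randomised and secondary. The primary result (relative risk 1.02) is untouched. This limits the weight of the point without removing it.

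Fourth, symptoms were not collected outside DEPIST-COVID screening (SAP 1.5), and community counts for symptomatic people are not tabulated separately. This limits a symptomatic comparison. It does not affect the asymptomatic one, because nurse-screened patients have questionnaire item 3.

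**Conclusion.** The mismatch is real and it determines the direction of the reported difference. Patients who are symptomatic by the protocol's own definition produce the +0.6 points. Without them the difference is -2.1 points using new diagnoses. Once excluded and unclassified patients are allowed for, it lies between about -2.1 and 0. The estimate never favours the EDs. Weighting the community rates in Table J2 to the EDs' share of screening gives 4.7%, which does not help the ED side.

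The safe conclusion is that the data give no support to a higher positivity in EDs among people without symptoms. A significantly lower positivity is not established, since at the 4.20% bound the interval includes zero.

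This rests on the questionnaire answer as the marker of symptoms, on Table E1 being a subset of Table D1, and on the community label meaning roughly the same thing. The -2.6 to -1.5 interval also assumes independence; the wider -3.7 to -0.4 rests on the borrowed design effect.

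**What to change.** In SAP section 1.1 and in the Changes to the analysis plan:
- Make the main version of this comparison screened patients who answered No to questionnaire item 3 against community tests in asymptomatic adults, and state that comparator.
- Keep new diagnoses as the numerator, in line with the Changes to the analysis plan. Drop indeterminate results from the denominator, and add a sensitivity row counting all positive tests.
- Show the mixed group only as a secondary row. Report a symptomatic comparison only if community counts by symptom status can be obtained.
- List the widening of the ED group among the changes in section 1.5.
- Revise Table J1, and Table J2 with its statement about three EDs, to match.

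The asymptomatic row needs only new wording and re-tabulation of data already collected. The costs are 130 patients with missing symptom status, smaller counts per ED, and a less favourable result.
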